**Process 2: Knowledge consolidation.**

The research nurse utilized Questionnaire Star to design “Picture-based cloze test”.

This test was specifically created to evaluate the patients' understanding of the rehabilitation process and to identify any areas where they might need further clarification or instruction. The picture-based format made it easier for patients to relate to the content, as it depicted real-life scenarios they might encounter during their rehabilitation journey. The results of these tests were then used to tailor subsequent educational materials and reinforce learning, ensuring that patients had a solid foundation of knowledge to support their recovery.

**Process 3: Error correction.**

Patients were given additional resources and materials to further reinforce their understanding of the rehabilitation process. This included detailed documents, and access to an online support group where they could share experiences and tips with others who were also undergoing rehabilitation. The aim was to create a community of support that extended beyond the hospital walls, providing patients with a sense of belonging and ongoing encouragement. The rehabilitation team also organized periodic webinars where patients could ask questions and learn from experts in the field, ensuring that their knowledge remained up-to-date and relevant to their recovery journey.

**Process 4: Answer questions and clarify doubts.**

The rehabilitation team also made themselves available for one-on-one consultations, providing personalized answers to any questions that arose during the rehabilitation process. This level of engagement helped to address concerns promptly and reinforced the patients' confidence in their ability to manage their recovery effectively.

**The processes above were continuous monitoring and feedback by research team.**

To ensure that the rehabilitation process was effective and that patients were progressing as expected, the research nurse implemented a continuous monitoring system. This involved regular check-ins with patients to assess their progress and to identify any challenges they might be facing. The feedback from these sessions was critical in adjusting the rehabilitation plan to better suit the individual needs of each patient. The team also used a feedback loop to incorporate patient suggestions into the program, making it more patient-centered and responsive to their needs. This iterative approach allowed for a dynamic and adaptive rehabilitation process that could evolve with the patient's changing circumstances and recovery milestones.

**4.3.2 Control group**

The control group received traditional health education. Patients were instructed to access an online manual titled 'Elbow Rehabilitation' by scanning a code using WeChat. The manual provided comprehensive information on elbow anatomy, common injuries, and rehabilitation exercises. It was designed to be user-friendly, with clear illustrations and step-by-step instructions to guide patients through their recovery at home. The control group's approach was more self-directed, with less personal interaction compared to the WeChat group, which received the additional support and resources described earlier.

Post-discharge, weekly follow - up calls were made to ensure the continuity of the recovery process. This group's progress was monitored through periodic phone calls, where they were asked to report on their symptoms and adherence to the rehabilitation exercises. The research team used this information to evaluate the effectiveness of the online manual and self-directed approach.

**4.4 Study Duration**

The duration of this study was 15 months.

**4.4.1 Study Outcome**

All datas were collected by using a standardized data collection form and process.

**4.4.1.1Primary Outcome**

The elbow range of motion (ROM) was measured by using a handheld goniometer and consisted of four angles: elbow flexion and extension, forearm pronation, and supination [41, 42]. The ROM was measured three times by a surgeon using three landmarks (the lateral epicondyle, the tip of the acromion process, and the middle portion of the wrist)., after which the average ROM was calculated.

**4.4.1.2 Secondary outcome measures**

The secondary outcomes were elbow function, quality of life and postoperative complications.

1. **Elbow function**

This was assessed using the Mayo Elbow Performance Score (MEPS), a validated scoring system that evaluates pain, range of motion, stability, and daily activities. Patients were scored at the beginning of the study and at the 1-week, 6-weeks and 12-weeks postoperative to determine any improvements.

1. **Quality of life**

This was measured using the was evaluated using the Short Form 36 (SF-36) [41]. Psysiological function was used in this study.

1. **Postoperative complications**

These were recorded and categorized as the formation of heterotopic ossification (HO), new onset or exacerbation of ulnar nerve symptoms, and repeat elbow stiffness. Elbow HO was classified into three grades: Grade 1, no functional limitation; Grade 2A, limited flexion and extension; Grade 2B, limited pronation and supination; Grade 2C, 2A combined with 2B; and Grade 3, ankylosis [43, 45]. The new onset or exacerbation of ulnar nerve symptoms could be observed by using the Dellon classification, which evaluates sensory (paresthesia, vibratory perception, and 2-point discrimination) and motor symptoms (muscle weakness and atrophy) [41,43]. Repeat elbow stiffness could be diagnosed by the ROM of the elbow [41,43].

**4.4.2 Clinical Assessments**

The clinical assessments were conducted by a team of experienced orthopedic surgeons. Any adverse events or complications were documented and managed according to the standard clinical protocols. The data collected from these assessments were then analyzed to evaluate the efficacy and safety of the surgical intervention being studied.

1. **The elbow range of motion (ROM)**

This was measured in degrees, with full extension considered as 0 degrees and full flexion as the maximum angle achieved without pain or discomfort. Pronation and supination were also measured, with the forearm in a neutral position for pronation and fully supinated for supination. The ROM data were then compared to the preoperative measurements to assess the improvement or deterioration in joint function post-surgery. The surgeons also evaluated the presence of pain during motion and its impact on the patient's daily activities. These clinical assessments provided a comprehensive overview of the patient's functional recovery and were crucial in determining the success of the surgical intervention.

1. **Mayo Elbow Performance Score (MEPS)**

The MEPS ranges from 0 to 100, with higher scores indicating better elbow function [42]. The score ranges from 0–100 points and is classified into four categories: excellent (90–100), good (75–89), fair (60–74), and poor (0–59)[11, 41, 42]. The MEPS is calculated based on four parameters: pain, range of motion, stability, and daily activities. Each parameter is assigned a specific number of points, and the total score is then derived from the sum of these points. The assessment of pain is based on the patient's subjective report and the surgeon's objective evaluation during movement. The range of motion is measured as described previously, with the addition of stability assessment, which involves checking for any signs of joint laxity or abnormal movement. Finally, the impact of the patient's elbow condition on their daily activities is evaluated, considering factors such as work, personal care, and recreational activities. The MEPS provides a standardized method for clinicians to quantify the functional outcome of elbow surgery and to communicate this information effectively to patients and other healthcare providers.

1. **Short Form 36 (SF-36)**

This is a self-rating scale consists of eight dimensions: physiological features, physiological function, somatic pain, general health, vitality, social function, affective function, and mental health. The Cronbach's α coefficient ranges from 0.65–0.94. Psysiological function was used in this study. Scores ranged from 0–100, with higher scores indicating better quality of life. The results are compared to norm-based scores to determine the extent of improvement or decline in various aspects of the patient's well-being. This tool is particularly useful in assessing the broader impact of elbow surgery on the patient's life, beyond just the physical function of the joint. By considering both the MEPS and SF-36 outcomes, clinicians can gain a more holistic understanding of the patient's recovery and tailor post-operative care and rehabilitation programs accordingly.

1. **Hastings and Graham classification**

The Hastings and Graham classification is a system that categorizes elbow heterotopic ossification based on the limitation of range of motion: Grade 1, no functional limitation; Grade 2A, limited flexion and extension; Grade 2B, limited pronation and supination; Grade 2C, 2A combined with 2B; and Grade 3, ankylosis [1].

The Hastings and Graham classification, when used in conjunction with the MEPS and SF-36, offers a comprehensive approach to assessing and managing elbow heterotopic ossification, ensuring that patients receive the most appropriate and individualized care.

1. **Dellon classification**

Which evaluates sensory (paresthesia, vibratory perception, and 2-point discrimination) and motor symptoms (muscle weakness and atrophy), provides a detailed framework for assessing nerve function in patients with elbow injuries. The classification system includes three grades, with Grade I indicating minimal sensory or motor impairment and Grade III representing severe impairment. This classification is instrumental in guiding treatment decisions and prognosticating recovery outcomes. By combining the Dellon classification with the Hastings and Graham classification, as well as the functional and quality of life measures provided by the MEPS and SF-36, clinicians can develop a comprehensive treatment plan that addresses both the physical and neurological aspects of the patient's condition. This multidimensional approach ensures that all factors influencing the patient's recovery are taken into account, leading to a more personalized and effective rehabilitation process.

1. **Repeat elbow stiffness**

The repeat elbow stiffness is a common complication that can occur after elbow surgery or trauma. It is characterized by a gradual loss of range of motion and can significantly impact a patient's ability to perform daily activities. The condition is often managed with a combination of physical therapy, medications, and in some cases, surgical intervention. Early identification and treatment are crucial to prevent the progression of stiffness and to optimize functional outcomes. Clinicians may use a variety of assessment tools to monitor the progression of stiffness and to guide treatment decisions. These tools include range of motion measurements, patient-reported outcome measures, and imaging studies to visualize the extent of the stiffness. The goal of managing repeat elbow stiffness is to restore as much function as possible and to minimize pain and discomfort, thereby improving the patient's overall quality of life.

**4.4.3 Statistical Method**

SPSS Statistics version 26.0 (IBM Corp) was utilized for the data analysis. The chi-square test was used to analyze sex, disease side, and the incidence of postoperative complications. The collected data were subjected to a comprehensive statistical analysis to evaluate the effectiveness of the intervention on elbow stiffness. The normality of the data was first assessed using the Shapiro-Wilk test. For variables that satisfied the normality test, parametric statistical methods were employed, including the paired sample t-test for comparing pre-intervention and post-intervention values. For variables that did not meet the normality assumption, non-parametric tests, specifically the Wilcoxon signed-rank test, were utilized. The changes in elbow range of motion (ROM), the Mayo Elbow Performance Score (MEPS), and the Short Form-36 (SF-36) health survey scores at each time point were analyzed using repeated measures analyses of variance (ANOVA). The results were presented as mean ± standard deviation (SD) for continuous variables and as frequencies and percentages for categorical variables. In cases where the data were not normally distributed, median values and interquartile ranges (IQRs) were reported. The level of statistical significance was set at a two-tailed P value < .05. All statistical analyses were performed using appropriate software to ensure accuracy and to provide a robust interpretation of the study findings.

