| **Main Exclusion Criteria** | 1. Patients with a history of psychiatric disorders or cognitive impairments that would interfere with the ability to comply with the study protocol.  2. Patients who have undergone previous elbow surgeries or have other medical conditions that could affect elbow function.  3. Pregnant women or those planning to become pregnant during the study period.  4. Individuals with known allergies to any of the medications or materials used during the surgical procedure.  5. Patients who are participating in other clinical trials simultaneously or have done so within the past 6 months. |
| **Allocation** | Eligible patients were split into two groups by admission time: the control group (56 patients enrolled from Jan.–Jun. 2021) and the WeChat group (56 patients enrolled from Jul.–Dec. 2021). |
| **Statistical Methodology** | The statistical analysis was conducted using SPSS software version 26.0. The primary outcome measures were elbow range of motion (ROM), which were assessed at baseline, at discharge, and at 1, 6, and 12 weeks post-operation. Secondary outcomes included quality of life, elbow function, and postoperative complications. The data was analyzed using descriptive statistics to summarize the demographic and clinical characteristics of the participants. Inferential statistics, including t-tests for continuous variables and chi-square tests for categorical variables, were used to compare the differences between the control and WeChat groups. Repeated measures analysis of variance (ANOVA) was conducted to evaluate the changes in ROM over time within each group and between the groups. The significance level was set at p<0.05 for all statistical tests. |
| **Safety** | Adverse events will be summarized for each group. The safety analysis will focus on the frequency and severity of any complications that arise during the study period. This includes, but is not limited to, infections, allergic reactions, and any other unexpected medical events that may occur. The safety data will be analyzed to determine if there is a significant difference in the incidence of adverse events between the control and WeChat groups. The results will be reported in accordance with the CONSORT guidelines for randomized controlled trials, ensuring transparency and completeness of the safety data. |

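### Section 4.4.3 names paired before-after tests, with a paired non-parametric fallback, under an effectiveness aim, and does not name the WeChat-versus-control contrast that the Summary uses

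*Protocol*

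**What the plan says.** Section 2.2.1 sets the primary objective as a comparison of the WeChat group with the control group.

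Section 4.4.3 presents its methods as a "comprehensive statistical analysis to evaluate the effectiveness of the intervention on elbow stiffness". For continuous outcomes it then names:

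- after a Shapiro-Wilk check, parametric methods "including the paired sample t-test for comparing pre-intervention and post-intervention values";
- for the other case: "For variables that did not meet the normality assumption, non-parametric tests, specifically the Wilcoxon signed-rank test, were utilized";
- a repeated measures ANOVA for ROM, MEPS and SF-36, with neither a group factor nor a group-by-time term mentioned.

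Its only test of independent groups is the chi-square test, for sex, side and complications.

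The Statistical Methodology row of the Protocol Summary reads differently. There, inferential methods, "including t-tests for continuous variables and chi-square tests for categorical variables, were used to compare the differences between the control and WeChat groups", and a repeated measures ANOVA looks at ROM within and between the groups. That row mentions no paired test, no normality check and no non-parametric test. The Result row of the Summary gives a between-group difference with CI and P value for the four angles, the Mayo score and SF-36.

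**The concern.** A paired t-test or signed-rank test asks whether patients changed from before to after. It does not ask whether one arm changed more than the other. Section 4.4.2 compares ROM with preoperative values, and section 1.1 describes the operation itself as aiming for flexion above 130° and extension below 10°. The before-after change in either arm therefore contains the surgical gain, and a significant result says nothing about the education.

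Two things are at stake. A reader of 4.4.3 could take a very small before-after P value as evidence for the WeChat programme. And an analyst who follows the non-normality rule in 4.4.3 is sent to a test that cannot compare two independent arms, because no two-sample rank test is named anywhere in the Protocol.

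**Working it through.** **Inputs.** Means and SDs come from the Summary's Result row, and 56 per arm from the Allocation row. All 56 are assumed analysed in each arm. The row does not say at which visit the later value was taken. The correlation r between baseline and later value is not reported, so it is derived in step 2 and then bounded in step 3.

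**Step 1: reproduce the plan's own figure.** The flexion difference in change is (124.2 − 71.5) − (114.4 − 71.7) = 52.7 − 42.7 = 10.0°, as stated. For each arm, SD of change = √(s0² + s1² − 2·r·s0·s1). With r = 0 and 110 df the 95% CI is 4.97 to 15.03, against the stated 4.9 to 15.1. A comparison of later values alone gives 9.8° (5.05 to 14.55). The reported result therefore fits a two-sample comparison of change scores.

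**Step 2: correlation implied by each reported CI.** Take r as common to both arms. Flexion: SE = (15.1 − 4.9)/2/1.982 = 2.573, so the two change variances sum to 56 × 2.573² = 370.9. The four squared SDs sum to 360.65, and 2·Σ(s0·s1) = 223.4. Hence r = (360.65 − 370.9)/223.4 = −0.05. The other outcomes are done the same way.

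**Step 3: paired t in the control arm**, which had no WeChat or scene-graphics education. Here t = mean change/(SD of change/√56). The worst case for a paired test is r = −1, where SD of change = s0 + s1.

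| Outcome | Control change | Implied r | SD of change | Absolute t | Absolute t at r = −1 |
|---|---|---|---|---|---|
| Flexion | +42.7 | −0.05 | 14.55 | 22.0 | 17.6 |
| Extension | −18.7 | 0.20 | 4.56 | 30.7 | 19.4 |
| Pronation | +30.1 | 0.16 | 7.74 | 29.1 | 19.8 |
| Supination | +33.8 | −0.05 | 10.81 | 23.4 | 18.2 |
| Mayo score | +16.9 | −0.03 | 7.52 | 16.8 | 13.0 |
| SF-36 | +31.0 | 0.14 | 12.12 | 19.1 | 13.2 |

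Even at r = −1 every P value is below 1e-17. In the WeChat arm the absolute t at r = −1 runs from 17.8 to 36.6. Both arms are significant on all six outcomes at any correlation.

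**Step 4: no education effect.** Both arms were simulated from the control flexion figures with r = 0. The paired t-test rejected in 100% of 4,000 runs and the signed-rank test in 100% of 1,000 runs. The two-sample test of change rejected in 4.4% of 4,000 runs, close to the nominal 5%.

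**Step 5: what it would take for the paired test to fail.** For control flexion, SE = 14.55/√56 = 1.94. With a critical t of about 2.00, the mean change would have to fall below about 3.9°. The education would have to cancel roughly 42.7 − 3.9 = 38.8° of the gain.

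**The case against.** The best defence is that 4.4.3 never makes the paired test the WeChat-versus-control test. The effectiveness sentence introduces the whole section. The paired t-test is offered as one method for one job, comparing values before and after. Between-group testing is stated in the Summary and reported in the Result row, and paired tests within arms can coexist with t-tests between arms. The large control-arm t values show that patients improve after surgery. They do not show bias or an inflated error rate in the between-group estimate, whose test rejected at about the nominal rate in step 4.

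Most of this stands, and it rules out three stronger readings:

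- *The Protocol has no between-group test.* It has: the Summary names t-tests between the groups and a between-group ANOVA for ROM.
- *A failed normality check leaves some angles with only a within-group test.* The ANOVA sentence in 4.4.3 is not conditional on Shapiro-Wilk, and the Summary's t-tests carry no normality condition.
- *The reported results rest on the paired tests.* Step 1 points the other way: the flexion figure matches a between-group comparison of change.

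The defence does not remove the defect in 4.4.3 itself. Under an effectiveness aim, the section names two tests that cannot answer the question and an ANOVA without its group term. Its only non-parametric alternative is unsuitable for independent arms. This is not merely detail left to an analysis plan, because the Protocol states a specific test and that test is the wrong kind. Nor do the two sections describe the same analysis: neither paired test is in the Summary, and the Summary's two-sample t-test is not in 4.4.3.

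**Conclusion.** The point holds as a defect of section 4.4.3 and of its agreement with the Summary. As tests of the education, the paired t-test and the signed-rank test are uninformative: control-arm absolute t is about 17 to 31 with correlations implied by the reported CIs, and at least 13 whatever the correlation. The range of 17 to 31 assumes a common correlation in both arms and CIs taken from change scores. The floor of 13 needs only the printed means and SDs and 56 patients per arm.

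A reader might say these tests are significant whatever the education does. That is true in practice but not literally, since a programme harmful enough to cancel nearly all the surgical gain would make them non-significant. The documents do not show that the reported between-group differences are wrong on this account.

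**What to change.** In section 4.4.3:

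1. Name one between-group analysis as the effectiveness test for each continuous outcome (four angles, MEPS, SF-36): the baseline-adjusted WeChat-minus-control difference with 95% CI at each of the 1-, 6- and 12-week visits. If it comes from a repeated measures model, state the group and group-by-time terms.
2. Fix that analysis in advance, so that it does not depend on a Shapiro-Wilk result.
3. For clearly non-normal data, give a two-sample rank test (Mann-Whitney) or a bootstrap interval as the sensitivity analysis, in place of the signed-rank test.
4. Keep the paired tests, if wanted, only as descriptive within-arm summaries.
5. Word the Summary's Statistical Methodology row and section 4.4.3 so that they describe the same analysis.

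The cost is the rewording of two paragraphs and a re-run in the same software. The baseline values are already collected.

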**5.Data**

**5.1 Data Collection**

The data collection process was meticulously designed to ensure the accuracy and reliability of the information gathered. A structured protocol was established to guide the collection of demographic information, medical history, and the specific outcomes of interest. Patients were enrolled in the study following a thorough explanation of the research objectives and the provision of informed consent. Data were collected at multiple time points, including baseline and at 1, 6, and 12 weeks post-operation, to capture the dynamic nature of elbow stiffness and its response to treatment. Standardized forms were used to record range of motion measurements, patient-reported outcomes, and any complications that arose. The data collection team underwent rigorous training to minimize variability and ensure consistency across all measurements. All data were entered into a secure electronic database to facilitate analysis and to protect patient confidentiality.

